### Economic evaluation

The economic evaluation will be carried out according to the intention-to-treat principle. Non-parametric bootstrapping (1000 replications) will be used to obtain 95% confidence intervals to estimate the uncertainty surrounding the cost differences, because cost-data are usually skewed to the right [57].

For the cost-effectiveness analysis, the incremental cost-effectiveness ratio (ICER) will be calculated by assessing the ratio of the differences in costs between the groups to the differences in effects between the groups. The ICER indicates whether the additional investments needed for the interventions gain at least one extra unit of effect compared with care as usual [57]. The cost-utility ratio will be calculated by the incremental costs divided by the difference in QALYs [39,58].

Bootstrapping with 5000 replications will be used to estimate the sample-uncertainty around the point estimates (ICER and ICUR). The bootstrapped ICERs and ICURs will be graphically presented on a cost-effectiveness plane. Furthermore, acceptability curves will show the probability that the employability intervention is cost-effective at a specific ceiling ratio, which is the maximum amount of money society is willing to pay to gain one extra unit of effect or a gain in quality of life [59]. Finally, the robustness of the different parameters on the cost-effectiveness calculation will be assessed by sensitivity analyses. Data processing will be done in SPSS 17.0 and bootstrapping will be carried out in Excel.

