**Methods/design:**

Per employability intervention 142 participants are needed whereof approximately 66 participants receiving the intervention will be compared with 66 participants receiving usual care. Based on the intervention-specific characteristics, a randomized control trial or a quasi-experiment with match-criteria will be conducted. Notwithstanding the study design, eligible participants will be employees aged 18 to 63, working at least 12 h per week, and at risk of work disability, or already work-disabled due to medical restrictions. The primary outcome will be the duration of sick leave. Secondary outcomes are health status and quality of life. Outcomes will be assessed at baseline and then 6, 12 and 18 months later. Economic costs will consist of healthcare costs and cost of lost production due to work disability, and will be evaluated from a societal perspective.

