#### Randomization/matching

In the case of randomization, the minimization method will be applied. Minimization aims to ensure an excellent balance for several prognostic factors in small groups [40]. Employees consenting to participate will be pre-stratified according to age (18-32 years, 33-48 years, 49-64 years), gender, and working hours (12-24 h/week, > 24 h/week). Since health care providers will treat participants in both the intervention and in the control groups, the study cannot be blinded. Matching i.e. formulating experimental and control groups on the basis of pairing participants on the basis of predetermined matching criteria will be used. These matched-criteria are age, working hours and health complaints. Thus, an employee in the intervention group will be matched to someone meeting the same criteria who will then act as a member of the control group.

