### Data analyses

#### Effectiveness

All statistical analyses, performed to distinguish differences between the control group and the intervention group, will be performed according to the intention-to-treat principle. This means that the participants will remain in the group they were allocated to at baseline. All data regarding primary and secondary outcomes will be analysed using descriptive statistics. To control for protocol deviations likely to cause bias, data will be analyzed using per-protocol analyses whereby outcomes will be compared between those participants who received at least one or a partial intervention session and the control group. With the aim of correcting for possible regression to the mean, the baseline value of the particular outcome variable will be added to the model. Days of sick leave in the year before the inclusion, measured at baseline, will be added as a potential effect-modifier.

Diagnosis and prognostic parameters can be confounders, thus the Cox regression analysis for confounders will be used to adjust for differences between control and intervention groups. If necessary, differences in baseline will be adjusted for prognostic dissimilarities. Missing data will be handled using SPSS missing value analysis on item level. Completely missing measurements will be handled using multiple imputation.

The primary dependent variable is days of absence from work. In order to estimate the number of absence days, survival analyses will be used. There are two reasons why we opted to use survival statistics. Firstly, the time to sustainable employability is unlikely to be normally distributed which will make parametric statistical analysis difficult or inappropriate. Increasing productivity can occur quite early, possibly within months, but can also, as expected in the care as usual situation, may not be prolonged or may even decrease again. Secondly, survival analysis accounts for dropout by the technique of censoring. Participants who drop out will have the same hazard of sustainable employment than those that remained in the study. The Cox Proportional hazard model will therefore be used to analyse the HR of the days of sick leave duration. Reduced sickness absence duration in calendar days will be analysed with the Kaplan Meier survival method, and the differences in absence duration between both groups will be tested with a log rank test.

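### No baseline adjustment is stated for incremental costs and QALYs, although effects are adjusted and some comparisons are matched rather than randomised

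*Protocol article*

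**What the plan says.** Two designs are allowed, depending on the intervention. The abstract says that "a randomized control trial or a quasi-experiment with match-criteria will be conducted". For the matched design, Randomization/matching states: "These matched-criteria are age, working hours and health complaints". Gender is a balancing factor under minimisation but not a matching criterion. Baseline utility, baseline costs and prior sick leave appear in neither list.

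The analysis is then described in two separate places.

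- **Data analyses, Effectiveness.** To correct for regression to the mean, "the baseline value of the particular outcome variable will be added to the model". Sick-leave days in the year before inclusion enter as a potential effect-modifier. For confounding, "the Cox regression analysis for confounders will be used to adjust for differences between control and intervention groups". A further sentence is conditional: "If necessary, differences in baseline will be adjusted for prognostic dissimilarities". One test carries no covariates: "the differences in absence duration between both groups will be tested with a log rank test".
- **Economic evaluation (the later section of that name, after Data analyses).** On costs it states: "Non-parametric bootstrapping (1000 replications) will be used to obtain 95% confidence intervals to estimate the uncertainty surrounding the cost differences". The ICER is "the ratio of the differences in costs between the groups to the differences in effects between the groups", and the ICUR is incremental cost over the QALY difference. The section also fixes 5000 replications for the ratios, the cost-effectiveness plane, the acceptability curves and the use of Excel for bootstrapping. It names no covariate. Its sensitivity analyses concern the parameters of the calculation, not confounding.

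**The concern.** Cost-effectiveness is the purpose of the study. The article accepts that diagnosis and prognosis can confound the effect comparison, and its Discussion concedes that selection bias cannot be ruled out. The same variables drive care use, absence and quality of life, so the case for adjusting effects applies equally to costs and QALYs.

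If the economic section is followed literally, an imbalance present at T0 enters the result in two ways. A QALY total over 18 months normally includes the baseline utility and whatever part of the gap persists. Higher care use or absence before inclusion also tends to continue during follow-up. A bootstrap of group differences reproduces the sampling spread around a biased centre, and the plane and acceptability curve inherit that centre. An adjusted effect estimate could then be reported beside economic ratios that answer a differently confounded comparison.

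**Working it through.** **Figures in the plan.** The article states no number for this point. The nearest figure is the sample size: 120 / (1 − 0.15) = 141.2, rounded up to 142, which reproduces. The 120 before dropout gives the 60 per arm used below.

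**Inputs.** From the article: assessments at 0, 6, 12 and 18 months; about 1:1 allocation; the friction cost method. Assumed, because the article gives none: trapezoidal area under the curve for QALYs; the baseline utility gap *d*; the gap *c* in 6-month baseline cost; the share *ρ* of a baseline gap that persists at follow-up; utility SD; EUR 20,000 per QALY.

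**QALY difference.** With 6-month spacing the weights are 0.25, 0.5, 0.5 and 0.25 year. With no true effect, the bias in an unadjusted difference is *d* × (0.25 + 1.25*ρ*). For *d* = 0.03:

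- gap gone by 6 months (*ρ* = 0): 0.03 × 0.25 = 0.0075
- half persists (*ρ* = 0.5): 0.03 × 0.875 = 0.026
- all persists (*ρ* = 1): 0.03 × 1.5 = 0.045

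At EUR 20,000 per QALY these are worth EUR 150, 525 and 900 per person. Over *d* = 0.02–0.10 and *ρ* = 0.5–0.7, the shift is 0.0175 to 0.1125 QALY.

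**Cost difference.** Three half-years follow baseline, so the bias is 3 × *ρ* × *c*. For *c* = EUR 500–2000 and *ρ* = 0.3–0.7 this is EUR 450 (3 × 0.3 × 500) to EUR 4200 (3 × 0.7 × 2000).

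**Absence.** A gap of 10 days per half-year that persists gives 10 × 3 = 30 days over 18 months. That is a ceiling for production-loss cost, because the friction cost method counts losses only for the period needed to replace the employee. The article does not give the length of that period.

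**Effect on the conclusion.** Simulated with 60 per arm, no true effect on costs or QALYs, *ρ* = 0.5, utility SD 0.22 and both baseline gaps favouring the intervention. Adjustment is by regression on baseline utility and baseline cost. P(CE) is the mean probability of cost-effectiveness at EUR 20,000 per QALY.

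| Utility gap | Cost gap (EUR, 6 months) | Unadjusted QALY difference | Unadjusted cost difference (EUR) | P(CE) unadjusted | P(CE) adjusted |
|---|---|---|---|---|---|
| 0 | 0 | −0.001 | 15 | 0.49 | 0.50 |
| 0.03 | 500 | 0.026 | −762 | 0.71 | 0.50 |
| 0.05 | 1000 | 0.043 | −1510 | 0.85 | 0.50 |
| 0.10 | 1000 | 0.087 | −1530 | 0.92 | 0.50 |

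Adjusted differences were within 0.001 QALY and EUR 20 of zero. This is the best case for adjustment, since the model contains exactly the variables that created the gap.

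**Could gaps this large arise?** The standard error of a baseline utility difference is SD × √(2/60): 0.027 for SD 0.15 and 0.055 for SD 0.30. A gap of 0.03 is therefore about chance size even under randomisation. Non-random allocation can add a systematic part.

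**The case against.** The strongest objection is that the article is silent rather than wrong. The definitions of the ICER and ICUR hold equally for adjusted differences, and covariates are often left to a fuller plan. A reader might infer that the article commits to comparing raw means. It does not: neither raw nor unadjusted appears in that section, and naming Excel for the bootstrap does not fix the estimator.

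Three further readings also go too far.

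- **That every part of the ratios is unadjusted.** The effect in the ICER is not defined and could come from the adjusted models. The gap is clearest for costs and QALYs.
- **That effects are adjusted throughout.** The log-rank test is not adjusted, and part of the adjustment is conditional.
- **That baseline imbalance passes in full into the conclusion.** Matching on health complaints plausibly removes some of it, lost earnings are computed as a change from baseline, the friction period caps absence costs, and some comparisons may be randomised.

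The argument from silence does not dispose of the point. A uniform method for economic evaluation is the article's declared subject, to be applied to every intervention. The economic section goes down to replication counts and software, while the article specifies adjustment only under Effectiveness. That asymmetry is in the document itself. It also remains true that all gap sizes above are assumptions and that the QALY method is not stated.

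**Conclusion.** The point holds in a limited form. The article states no baseline adjustment for incremental costs or QALYs, plans it for effects, and allows non-randomised comparisons matched on three factors only. Followed as written, the economic result would carry whatever imbalance in baseline utility, baseline costs or prior sick leave the matching leaves behind, and the bootstrap intervals would not show it.

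Under the stated assumptions, modest gaps matter: a utility gap of 0.03 with a EUR 500 cost gap moves the probability of cost-effectiveness from 0.50 to 0.71 with no true effect. The direction depends on which group starts better off, so gaps against the intervention would lower the probability instead. The documents do not show that such gaps exist, nor that an unadjusted analysis is intended. The change is worth making because it improves the method at little cost.

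**What to change.** In the later Economic evaluation section, state that:

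1. Incremental costs and QALYs are estimated by regression, adjusted for baseline utility (QALYs), baseline costs (costs), prior-year sick leave and the confounders used in the effect analysis.
2. The regressions are re-fitted within each bootstrap replicate. Costs and effects are resampled together, and matched pairs are the resampling unit in the quasi-experiments. The plane and acceptability curves use the adjusted differences.
3. The ICER uses an adjusted effect, expressed as a difference in a named unit, since a Cox hazard ratio is not itself such a difference.
4. Unadjusted differences are reported alongside.

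A joint model such as seemingly unrelated regressions is one acceptable option, not a requirement.

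The cost is more programming than an Excel bootstrap of group means. No new data are needed: the questionnaire combining the EQ-5D-5L, TIC-P and PRODISQ items is given at T0, and prior-year sick leave is already recorded at baseline. Adjustment removes only measured imbalance, so the article's caution about selection bias should stay.

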## Discussion

This study protocol provides detailed information on how to assess the effectiveness and cost-effectiveness of employability interventions among employees with work disabilities or employees at risk of becoming work-disabled due to health complaints. The results derived from these economic evaluations can benefit the individual employee, the employer and the broader occupational health practice sector because illness duration, care consumption and costs of lost productivity are expected to decrease if the employability intervention is cost-effective. For society as a whole, cost-effective employability interventions are attractive since they are expected to increase labour participation and public health. Furthermore, we feel that productivity is the key to higher economic growth as we are facing an ageing population.

A limitation of this study-design is the generalisability to other countries. The employability interventions are specifically tailored for the Dutch context in which they will be implemented. When applying these interventions in other countries, specific characteristics of the population in relation to the societal, political and cultural context in which the interventions are to be used should be taken into account. Although international generalisability might be restricted and require adaptation to the intervention, lessons can be learned and implementation advice given to those engaging in future work.

Selection bias cannot be ruled out in this design because we ask the healthcare provider to select employees to participate in our study. As a consequence, healthcare providers cannot be blinded. Furthermore, the consultation with the health care provider might change the participants' point of view on work disability. This 'Hawthorne effect' will be born in mind and might overestimate or underestimate the effect of the intervention. However, we feel that minor interactions such as the provision of information about the study will not be an important source of bias.

The strengths of this pragmatic design looking at the cost-effectiveness of employability interventions versus usual care, is the comparison under 'real life' circumstances of the intervention and control variables. Resource use is self-reported by participants and will be collected separately from the unit costs or prices of those resources. We will keep in mind the possibility that health care and intervention providers in different settings may wish to apply their own prices to the units of resource use. Furthermore, due to the standard recall period of 6 months, an adequate estimation of resource use is linear over time. This linear time trend restricts overestimation and underestimation of resource use between two consecutive measurement moments. An additional strength of this design is the inclusion of losses due to sick leave and the costs of using health care facilities together with productivity losses during working periods whilst unwell (presenteeism). In developing the methodology, we kept in mind the possibility that the employability and usual care interventions may have different effects on the component of reduced productivity while at work and therefore capture these. Besides internal validity, external validity of the results of the economic evaluation is reached by analysing the data from a societal perspective. We can split the calculated cost-effectiveness from the societal perspective to other perspectives, e.g. employee perspective, organisational perspective, etc.

To conclude, the research design provided in this article will be applied to each employability intervention included in the CASE-study. The CASE-study is the first study assessing the cost-effectiveness of different employability interventions. In addition, this design might contribute to new and better guidelines in the conduction of future economic evaluations in the occupational health sector. The results of the CASE-study will become available between 2012 and 2014.

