#### Participants

Employees eligible for participation in the study will be work-disabled or at risk of work disability due to medical restrictions. In order to identify these employees, we will use employer registration forms, registrations with health care organizations and insurance companies, and registration forms from those providing the intervention. Employees eligible for inclusion will be 18 to 63 years of age, perform paid labour for at least 12 h per week, and are able to communicate in Dutch. Reasons for exclusion are absenteeism for 1.5 years or longer, fulltime students with a student job, informal caregivers and/or volunteers.

In order to recruit a sufficient number of eligible employees, one or more health care providers providing an employability intervention will screen service users for inclusion in the study. When appropriate, information on the research will be provided to the patient. This will be done orally by the health care provider, possibly supported by a handout containing contact information for the researchers, what is expected of participants, privacy concerns, and so on. A self-completion card will be attached to each flyer (handout) consisting of a short checklist for inclusion and informed consent form for signing. The employee is requested to fill in the short checklist, sign the informed consent form, and send these back to the researcher. Participants will have at least 1 week to consider their participation in the study before signing the informed consent form. Participants will be screened for exclusion by the researcher on the basis of answers provided on the checklist. If an employee meets all the selection criteria and is willing to sign the consent form, randomization or matching will then place. Before the intervention starts, the first (baseline) measurement occurs. An email with a login code is sent to all participants, and they will be asked to fill in the baseline questionnaire. The questionnaire for the intervention group is identical to the one for the control group.

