#### Study design

As suggested by Drummond et al. (2001), a randomized controlled trial (RCT) remains the standard design for evaluating the relative effect of candidate interventions [39]. However, due to practical reasons, randomly assessing participants to the employability intervention or care as usual is not always possible in the CASE-study. Employers and occupational physicians are legally obliged to offer sickness absence guidance, and to do so, they refer employees to one or more employability interventions. Thus, a quasi experiment, comparing employees who are allocated to an experimental intervention in a non-random manner with those non-randomly assigned to a conventional intervention is regarded as the next best study design. Unlike an RCT, a quasi experiment consists of a control group derived from a large non-equivalent population. The variables are not manipulated, and participants are selected on the basis of matched criteria with those in the non-intervention group. Randomisation is not used therefore, and participants/control members are selected on the basis of their having an equal chance of demonstrating a causal relationship between the intervention and its outcomes for the control or experimental intervention. Both quasi experiments and RCTs are acceptable for the economic evaluation of employability interventions. The anticipated flow of subject enrolment in a quasi experiment or RCT is shown graphically in Figure 2.

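### Providers choose which of their own clients are invited; in the quasi-experiments this admitted selection bias can move the hazard ratio in either direction, and a consecutive-approach rule with a log would limit it cheaply

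*Protocol article*

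**What the plan says.** All references are to the protocol article.

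- **Who selects.** Under Participants, "one or more health care providers providing an employability intervention will screen service users for inclusion in the study". The same section continues: "When appropriate, information on the research will be provided to the patient". No rule says when that condition is met.
- **The researcher's part.** "Participants will be screened for exclusion by the researcher on the basis of answers provided on the checklist". This check reaches only people who were approached and returned the card.
- **Other sources.** To identify employees, "we will use employer registration forms, registrations with health care organizations and insurance companies", together with the intervention providers' own registration forms. The article does not say that these registers replace or check the provider's choice.
- **Controls.** Under Study design, "a quasi experiment consists of a control group derived from a large non-equivalent population". Under Randomization/matching, "These matched-criteria are age, working hours and health complaints".
- **Analysis.** Under Effectiveness, "the Cox regression analysis for confounders will be used to adjust for differences between control and intervention groups". The baseline value of the outcome enters the model, and sick-leave days in the previous year enter as a potential effect-modifier.
- **Admission.** In the Discussion, "Selection bias cannot be ruled out in this design because we ask the healthcare provider to select employees to participate in our study". The text then turns to provider blinding and the Hawthorne effect, and judges that giving study information is not an important source of bias. How clients are chosen is not taken up again.

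**The concern.** The article fixes a recruitment rule and names the bias that the rule creates, yet keeps the rule. If providers invite clients partly on how they expect them to fare, the intervention group differs from controls on something that age, hours and type of complaint do not describe. No later analysis can recover clients who were never approached and never logged.

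At stake is the primary comparison of sick-leave duration in the evaluations run as quasi-experiments. The cost-effectiveness ratios rest on the same groups, so the same bias would reach them.

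**Working it through.** **1. Where the bias can act.** In the Participants section, consent and the researcher's check come before randomisation. In a randomised evaluation the provider's choice therefore affects both arms alike, and its main consequence is for generalisability. In a quasi-experiment the control group has a different source, so nothing guarantees that the same filter acted on both groups.

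**2. The plan's own figures.** For HR 2.0, two-sided 0.05, 80% power and 1:1 groups, the events needed are 4 × (1.96 + 0.84)² / (ln 2)² ≈ 65.3, so 66. The stated 120 employees then imply an event fraction of 66/120 = 55%. The article gives no event fraction, so 120 is consistent with its inputs but cannot be derived from them alone. Dropout of 15% gives 120/0.85 = 141.2, so 142, as stated. I use 60 per group and 66 events below. The article ties this calculation to the Best Practice evaluations.

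**3. Assumptions (none is in the article).** The intervention has no effect. An unmeasured trait multiplies the return-to-work rate by g = 2 or 3. It is present in p0 = 50% of controls and p1 = 60, 70 or 80% of intervention employees. It is unrelated to the matched and adjusted variables.

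**4. Spurious hazard ratio.** At the start of follow-up, HR = [1 + (g − 1)p1] / [1 + (g − 1)p0].

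- g = 2: 1.6/1.5, 1.7/1.5, 1.8/1.5 = 1.07, 1.13, 1.20.
- g = 3: 2.2/2.0, 2.4/2.0, 2.6/2.0 = 1.10, 1.20, 1.30.

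A Cox fit over about 18 months gives nearly the same: 1.08, 1.14, 1.21 and 1.10, 1.22, 1.35.

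**5. False significance in favour of the intervention.** The normal approximation is P = 1 − Φ(1.96 − √(66/4) × ln HR), using the hazard ratios from the formula in step 4. Simulated log-rank tests (5,000 trials per setting, 55% events) agree closely.

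| g | p1 | HR (formula) | Approximation | Simulation |
|---|---|---|---|---|
| none | 50% | 1.00 | 2.5% | about 2.3% |
| 2 | 60% | 1.07 | 4.5% | 4.7% |
| 2 | 70% | 1.13 | 7.3% | 7.4% |
| 2 | 80% | 1.20 | 11.1% | 12.6% |
| 3 | 60% | 1.10 | 5.8% | 6.7% |
| 3 | 70% | 1.20 | 11.1% | 13.5% |
| 3 | 80% | 1.30 | 18.6% | 22.8% |

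More events make it worse. If 80% of controls return, the two 80% rows rise to about 17% and 35%.

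**6. The opposite direction.** If the trait is rarer in the intervention group (40, 30 or 20% against 50%), the formula gives HR 0.93, 0.87, 0.80 for g = 2 and 0.90, 0.80, 0.70 for g = 3. In simulation, false significance against the intervention is then 4.9, 8.4, 13.2% and 6.6, 14.4, 27.1%.

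**7. Against the article's own success criterion.** The primary outcome section calls an intervention effective when return to work is twice as quick. Reading this as an observed HR of at least 2.0, the chance with 66 events is 1 − Φ(√(66/4) × (ln 2 − ln HR)). This is 0.2% without bias, 0.6% at HR 1.08, 2.1% at 1.21 and 5.5% at 1.35.

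**The case against.** **Only one group may not be filtered.** The article describes a single recruitment path, after which either randomisation or matching follows. It also says that providers treat participants in both groups, though it says so to explain the lack of blinding. Who approaches controls is not stated, and the flow figure is not shown. The text also does not say which evaluations are quasi-experimental. This stands: a one-sided filter is possible, not established.

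**Direction.** A reader might infer that providers pick clients who will do well, so that the bias favours the intervention. No passage says this. Employers and occupational physicians refer employees to the interventions, and they could equally send harder cases.

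**Covariates.** A reader might infer that motivation and expected recovery are excluded from adjustment. The article names diagnosis and prognostic parameters without listing them, and the full list belongs in an analysis plan that is not shown. Baseline sick leave and self-rated health might partly stand in for such traits. What remains is that adjustment reaches only what is measured.

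**Conflict of interest.** A reader might infer that the Best Practice developers recruit for their own evaluation. The article says that these organisations developed the interventions, not that their staff recruit. It also says that the evaluators are unconnected with the developers. The concern needs only the stated fact that intervention providers do the screening.

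**Condensed article.** Approach rules and screening logs often sit in a full protocol, and the condition for informing clients might simply mean that they are eligible. That would settle the matter if the Discussion did not say that the provider is asked to select employees and that bias follows. The rule and its consequence are both on the page.

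**Conclusion.** The concern holds in limited form. Provider discretion over invitation is a stated rule with an admitted bias and no remedy. In the quasi-experimental evaluations it can shift the HR either way. In the randomised ones it mainly limits generalisability.

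Under the assumed trait, the spurious HR is about 1.1 to 1.35, and false significance in favour of the intervention is roughly 5-25% instead of 2.5%. The mirror-image assumption penalises the intervention to a similar degree. These figures rest wholly on the assumed trait effect, its prevalences, its independence from the adjusted covariates, and an event fraction near 55%.

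Two stronger readings are not supported: that the results will favour the interventions, and that the bias could by itself account for an HR of 2.0. This is a worthwhile and inexpensive improvement, not a defect that invalidates the design.

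**What to change.** In the Participants section, replace the discretionary condition with a rule: every consecutive service user who meets the written criteria is given the flyer and card. Apply the same rule to whoever approaches controls, and say who that is.

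Providers keep an anonymous log of eligible clients not approached. It records the reason and basic characteristics (age, gender, working hours, complaint), and current sick-leave status where already registered. Report the log for each evaluation. The researcher should not receive identifiable intake lists of people who have not consented.

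The cost is a sentence or two in the protocol and slight extra administration for providers. The rule removes discretion over study invitation and makes remaining selection visible. It does not remove bias from referral into the intervention or from the non-equivalent control source, so the Discussion should keep both as stated limitations.
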